## **1. SUMMARY**

Amref Health Africa Tanzania is implementing a pilot program in Shinyanga Region, Tanzania to integrate maternal, newborn and child health (MNCH) and prevention of mother to child transmission (PMTCT) services using community health workers (CHWs). The foundation of the multi-pronged intervention is linkage of CHWs to health facility staff for mentorship, supportive supervision, and coordination of tasks. In addition, CHWs will distribute the “Action Birth Card”, an interactive planning tool that links MNCH services delivered at the community level, such as breastfeeding counseling, to PMTCT and human immunodeficiency virus (HIV) treatment and care services delivered at the facility. The card will be targeted to both HIV-infected and uninfected pregnant women and asks them to define and overcome barriers to reproductive health services related to PMTCT and WHO’s core health indicators. Furthermore, CHWs in the intervention will provide monthly adherence counseling to women on antiretroviral therapy (ART) and will coordinate with health facilities to trace HIV-infected pregnant women who are lost to follow-up. Together, these strategies will newly integrate community-based MNCH services with HIV prevention, treatment, and care, bridging the gap between community and facility, and enhancing the potential benefits of Option B+.

Using a cluster randomized design, we will evaluate whether this approach: 1) results in earlier initiation of ART; 2) increases the proportion of HIV-infected pregnant women who are retained in care; and 3) increases adherence. We will also examine whether there is impact heterogeneity depending on women’s intensity of exposure to the intervention, and we will determine whether the intervention is acceptable and feasible for CHW, health facility staff, and pregnant and postpartum women. The results will be germane to local and regional authorities,

the Ministry of Health and Social Welfare, community organizations, and donors about whether this strategy can improve outcomes in the HIV care continuum.

## 2. PROBLEM STATEMENT

Globally, the number of children born with HIV-infection declined 35% during 2009-2012, a reduction partly attributable to antiretroviral (ARV) prophylaxis preventing 670,000 children from acquiring HIV infection in low- and middle-income countries during this period. However, despite this substantial achievement in PMTCT, there are still significant challenges facing the global effort to achieve UNAIDS' goal of "virtual elimination" of mother-to-child transmission (eMTCT) by 2015. To prevent transmission to their infants, HIV-positive pregnant women need to receive a series of services including antenatal care (ANC), HIV testing, disease staging, and ART or ARV prophylaxis. In addition, HIV-exposed infants should receive ARV prophylaxis, be tested for HIV infection, be exclusively breastfed for the first 6 months of life, and receive cotrimoxazole prophylaxis to prevent opportunistic infections. Although these services have been shown to reduce the risk of MTCT to <5% in breastfeeding populations and <2% in non-breastfeeding populations, in sub-Saharan Africa, 49% of HIV-infected pregnant women are lost between ANC registration and delivery and miss some or all of the essential PMTCT services. Consequently, only 57–70% percent of pregnant women living with HIV receive ART or ARV prophylaxis, one of the key steps of the cascade.

Increasing retention in the PMTCT cascade is particularly critical in high-burden, priority countries like Tanzania, where 6.2% of women aged 15-49 are HIV-positive and nearly one quarter of pregnant women living with HIV do not receive ARVs/ART for PMTCT. Notably, in Tanzania, achievements in PMTCT could have important impacts on the national epidemic, as 1 out of every 5 new HIV infections are due to mother-to-child transmission – an estimated 36,225 infections per year. In September 2013, Tanzania began rolling out 'Option B+' to all 6,270 reproductive and child health (RCH) facilities, the PMTCT strategy whereby HIV-infected pregnant women receive ART throughout their lives regardless of clinical stage. By simplifying service delivery, drug regimen, and reducing the number of steps that mothers need to negotiate (such as CD4 testing), Option B+ is expected to improve retention in the PMTCT cascade. However, the postulated benefits of Option B+ are predicated on mothers remaining on lifelong ART, starting at the time of HIV diagnosis. Thus, a critical unresolved issue is whether *asymptomatic* women who learn their HIV status during pregnancy will initiate and adhere to ART under Option B+.

## 3. BACKGROUND AND REVIEW OF LITERATURE

### *PMTCT & Option B+*

Malawi was the first to implement the Option B+ strategy, and the initial monitoring and evaluation data were encouraging: Option B+ dramatically increased ART coverage among HIV-infected pregnant women, among whom 77% continued to receive treatment at 12 months, comparable to 80% of adults in the national program. However, more recent cohort data paint a decidedly less optimistic picture, as Option B+ patients who started ART during pregnancy were five times more likely to never return after their initial clinic visit compared to women who started ART because they were treatment eligible. In the same analysis, pregnant women who started ART on the day of HIV diagnosis had the highest loss to follow-up rates. Furthermore, a meta-analysis of 51 studies, including over 20,000 HIV-infected pregnant and postpartum women, found that adherence (80% or higher) was a modest 53% in the postpartum period compared to 76% antepartum. Together, these data highlight the central challenge for eMTCT

and keeping women alive: preventing attrition from the treatment and care cascade and achieving high levels of adherence to ART.

### *Evidence Supporting Community-Based MNCH & PMTCT Integration*

Effectiveness of Facility-Based MNCH and PMTCT Integration: The integration of *facility-based* MNCH and PMTCT services is recommended by WHO and PEPFAR. A systematic review found that ART integration into MNCH facilities significantly improves ART uptake (RR: 1.37, 95% CI: 1.05–1.79). However, only one study has evaluated the effect of facility-based integration of MNCH and PMTCT on retention in care and no studies have evaluated ART adherence.

### *Effectiveness of CHWs for HIV-Related Outcomes*

In the HIV/AIDS realm, rigorous data on the effectiveness of integrating CHWs into HIV/AIDS treatment and care services are scarce. Although CHWs have been used to perform a variety of HIV/AIDS related activities including HIV testing, behavior change counseling, adherence support, and delivery of ART, a 2013 systematic review of the effectiveness of integrating CHWs with HIV care in sub-Saharan Africa found a weak evidence base. Of the 21 studies identified, five were qualitative, only 3 were randomized trials, and the majority of observational studies lacked control groups. Nevertheless, the findings from several higher-quality studies suggest the potential of integrating CHWs with HIV treatment and care. A cluster randomized trial in Uganda found that a community-based peer health worker intervention cut loss to follow-up rates at 24 months in half, from 4.4% to 2.1%, and decreased virologic failure rates ≥96 weeks into ART. Positive benefits on retention in care were also reported in quasi-experimental studies of CHW in Zambia, South Africa, and Malawi. In the South African study, ART patients with CHW adherence support had higher treatment pickup rates (95% vs. 67%, p=0.02) and were more likely to have a suppressed viral load after 6 months of treatment (70% vs. 30%, p<0.01). In addition, a home-based HIV-care strategy in Uganda using lay health workers was found to be as effective as a clinic-based strategy on viral suppression after 6 months of ART. The benefits observed in these studies may be because CHWs can help to demystify HIV, counteract stigma, and “bridge” the community and health facility.

### *Effectiveness of CHWs for PMTCT Outcomes*

In the proposed study, we hypothesize that the new integration of community-based MNCH services with PMTCT using CHWs will increase demand for ART among HIV-infected pregnant and breastfeeding women and will improve retention in care and adherence to ART. This hypothesis is bolstered by a small but growing body of evidence that such a strategy can be effective and also help to mitigate the health workforce crisis. In South Africa, mothers in the *Philani* program who received antenatal and postnatal home visits by CHWs were more likely to administer infant nevirapine at birth, correctly treat infants with zidovudine, and practice one feeding method for the first 6 months of the infants life. Overall, the odds of completing all services in the PMTCT cascade was nearly twice as high in the CHW intervention group compared to standard care. Also in South Africa, the *Goodstart* study found that CHW visits to pregnant and postpartum women increased exclusive breastfeeding among HIV-infected women and increased infant weight and length-for-age z-scores, although no differences were found for MTCT or HIV-free survival. Similar increases in PMTCT service utilization were observed in Malawi's *Tingathe* PMTCT programme, a CHW-based patient case management intervention. Although these studies are promising, these studies have a clear focus on preventing infant infections and improving infant health; none evaluated whether the mother was retained in care after her baby was delivered and whether she was adherent to ART. Furthermore, none have been conducted since the implementation of Option B+, which is a new and integrative approach to PMTCT with specific challenges for health care delivery.

In summary, the integration of ART services with maternal, newborn, and child health services (MNCH) is essential for PMTCT and has been demonstrated to improve ART coverage among HIV-infected pregnant and postpartum women. However, despite the proven effectiveness of delivering MNCH and other health services at the community level, there is a paucity of evidence on the effect of integrating MNCH and PMTCT services using CHWs. CHWs are integral members of the health system who have received training to promote health or to carry out some healthcare services, but who are not healthcare professionals. It is well known that CHWs can enhance the reach, coverage, and quality of HIV services delivered to the general population, but specific evidence for leveraging this essential cadre to link community-based MNCH services with the PMTCT cascade is small and primarily focused on infant outcomes. Integration of community-based MNCH services with PMTCT is especially critical because Tanzania is scaling up 'Option B+', a PMTCT strategy whereby HIV-infected pregnant and breastfeeding women are immediately initiated on lifelong ART after diagnosis. Given the significant potential for loss to follow-up after ART initiation, coupled with the high workload for health care workers, there is a strong argument for integrating community-based MNCH activities with PMTCT services using CHWs, especially adherence counseling and tracing pregnant women who never sought care or who fell out of care.

#### **4. STUDY SETTING AND RATIONALE**

Our study will be conducted in Shinyanga, one of Tanzania's 30 regions in the northern "Lake Zone" where HIV prevalence is 7.4% (8.1% among women). Under Tanzania's Reproductive Child Health Platform Approach and Option B+, ANC, postnatal care, and HIV treatment and care are now provided in the majority of Tanzania's 6,270 reproductive and child health (RCH) clinics. There are approximately 12,000 CHWs in Tanzania, including 1,512 CHWs in Shinyanga Region who serve 490 villages. Under the current structure, however, CHWs in Shinyanga do not participate in any activities related to the provision of HIV care for HIV-infected pregnant women, PMTCT, or Option B+.

The current study would connect these two separate programs and subsequently evaluate the effectiveness of providing Option B+ through CHW care. While previous studies have found CHWs to be effective, they have a clear focus on preventing infant infections and improving infant health; none evaluated whether the mother was retained in care after her baby was delivered and whether she was adherent to ART. Furthermore, none have been conducted since the implementation of Option B+, which is a new and integrative approach to PMTCT with specific challenges for health care delivery.

#### **5. DESCRIPTION OF THE INTERVENTION**

##### ***Mama na Mtoto Pamoja (Mother and Child Together)***

The intervention, implemented by our partner Amref Health Africa Tanzania, will integrate community-based MNCH and PMTCT services by implementing the following policies, activities, and tools in 15 communities:

1. Formal Linkage of CHW to RCH clinics: As noted above, although an informal relationship exists between CHWs and a single health facility for referral purposes in relation to maternal and child health services, there is currently no process for CHWs to review activities with clinic staff, receive mentorship, and determine which women have been lost to follow-up. We will assign each CHW to a nurse in the RCH clinic for a monthly meeting to discuss their activities. This will overcome the limitations of the current model whereby CHW are not engaged with health facility staff for supervision and supportive mentorship.

2. Action Birth Card: The “Action Birth Card” is an interactive, integrated health planning tool distributed by CHWs that links MNCH services delivered at the community level to PMTCT and HIV treatment and care services delivered at the facility. It asks pregnant and breastfeeding women to define and overcome barriers to reproductive health services related to PMTCT and WHO’s core health indicators for women and children’s health. Furthermore, the card facilitates discussion between CHWs and their clients and serves as a user-friendly record of completed services and behaviors (e.g., breastfeeding) for maternal health, PMTCT, HIV treatment, family planning, and infant health.

The Action Birth Card will be distributed by CHWs at their first meeting with pregnant and postpartum women, discussed at all subsequent monthly meetings, and collected after the infant has been tested for HIV infection, 6-8 weeks postpartum. The card, containing health content relevant to *all* women, will be targeted to both HIV-infected and uninfected women to prevent stigma.

3. Tracing of treatment defaulters: At their monthly meetings with RCH staff, CHWs will review the ART register to identify women who missed scheduled appointments and those who are lost to follow-up according to the local definition: non-attendance at three successive scheduled appointments with two unsuccessful follow-up attempts. CHWs will attempt to contact these women via mobile phone or home visit and re-engage them in care. CHWs will provide updates to the clinic about their progress and will coordinate tracing activities with those of the clinic (if any).
4. Adherence counseling for HIV-infected women on ART: CHWs will use the existing adherence counseling manual used by community-based home based care volunteers for people living with HIV, with additional messaging customized for asymptomatic women (as many recently diagnosed pregnant women will be asymptomatic). Adherence counseling will be conducted during the monthly CHW home visits.

The intervention’s theory of change is shown below in **Figure 1**, including the process and impact indicators that will be measured as part of the impact evaluation. Currently, CHWs in Shinyanga Region (and elsewhere in Tanzania) refer pregnant women to ANC in addition to other health promotion activities. Once registered for ANC, pregnant women may or may not complete the services in the PMTCT cascade, including starting and adhering to ART (if HIV-infected), and they may disengage and re-engage in care. In the current study, we will implement an intervention to integrate community-based MNCH services and PMTCT using CHWs. We hypothesize that this approach will result in HIV-infected pregnant and postpartum women initiating ART earlier as well as better retention in care and improved adherence.

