## 6. 2 Impact and Process Indicators

### Impact Outcomes:

1. Timing of ART initiation: The timing of ART initiation among HIV-infected pregnant women according to gestational age (The number weeks since the first day of the last menstrual period (LMP)). We hypothesize that women in intervention communities will initiate ART earlier than women in comparison communities.
2. Retention in care: Whether an HIV-infected pregnant or postpartum woman on ART is still in care 90 days postpartum (binary 1/0). In Tanzania, postpartum women on ART are typically scheduled for clinical monitoring for their own health at 7, 28, and 42 days (6

week postnatal visit) and then every 30 days thereafter until transfer to the HIV clinic at 18 months. We define retention as a woman who attended her scheduled visit between 60-90 days postpartum.

3. Adherence: We will measure adherence with the medication possession ratio (MPR), the proportion of days when ART was prescribed and an individual is in possession of ART (determined with pharmacy dispensing data). MPR is associated with short-term virologic outcomes. We will determine the proportion of women with MPR  $\geq 95\%$  at 90 days postpartum (binary 1/0).

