## 7.2. Data Sources

Data will be abstracted from the following sources, using the woman's clinic identification number (clinic ID) as the unique code to link across data sources:

- **CHW logs:** CHWs maintain standardized logs of pregnant and postpartum women in their catchment area. At the start of the study, we will modify the log form to include women's clinic ID. We will retrospectively abstract the clinic ID along with demographic data about both HIV-infected and uninfected women in the baseline or endline cohorts, as CHW in comparison villages may not know women's HIV serostatus. Note that this is a significant strength of our study, as we will have a community-based measure of pregnant women, including women who do not utilize RCH services.
- **ANC register:** Contains information about all women who booked for ANC, including number of visits, HIV testing results, health facility delivery, and attendance at the postnatal visit. We will abstract these data for each woman in the baseline or endline cohort and match their health information with CHW log information.
- **ART register:** Contains information about HIV-infected pregnant or postpartum women who are initiated on ART at RCH clinics. For all HIV-infected women in the baseline or endline cohorts, we will match them to the ART register to determine whether they initiated ART and attended visits.
- **CTC2 Cards:** Contains individual medical record data for HIV-infected women. We will abstract data from these cards as needed, to supplement data in the ART register.
- **Pharmacy logbook:** Contains ART pick-up dates and quantity for HIV-infected women.

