All three indicators will be measured primarily from ANC records, though we will also back check these records with CHW logs to ensure accuracy and quality of the data. We will analyze all three measures through difference in difference strategy in order to capture differences in outcome between the control and treatment groups.

**7.5. Evaluation Question #2:** Is the impact of integrating community-based MNCH and PMTCT

*services on retention in care and adherence greater among women who had more contact with CHWs?*

To answer this question, we will monitor the CHW logs to measure (a) the duration of visits with CHWs and (b) the frequency of visits (per week, per month). We will then compare the frequency and duration of visits to each woman's retention in the program, and their level of participation (measured through adherence to ART) to find the correlation between CHW contact and participation.

*7.6. Evaluation Question #3: Is integration of community-based MNCH and PMTCT services acceptable and feasible for CHW, health facility staff, and pregnant and postpartum women, and are there potential spillover benefits on other maternal health outcomes?*

We will conduct a mixed methods process evaluation, including quantitative analysis of process outcomes feedback from stakeholders (two facility personnel, five CHWs, five clients, two Amref staff), and in-depth interviews with women, in order to better understand the effectiveness and feasibility of the intervention. We will focus our efforts on answering the following key questions:

- a. Was the intervention implemented as intended? Was there heterogeneity in implementation? Were standard operating protocols followed consistently and correctly?
- b. Were there community- or facility-level factors that influenced the success of the intervention? Was the intervention impeded by the time availability of CHW or facility staff?
- c. Did the intervention motivate pregnant and postpartum women? How? What aspects were motivating and why? Did the intervention inadvertently increase stigma?
- d. What were successful or challenging aspects of the intervention throughout the causal chain (**Figure 1**)? What could be improved?

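### The package has CHWs review the ART register monthly in intervention communities, and that register is the operative retention record, so recording could improve in one arm only; the size is unknown and one uniform source rule would limit it

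*Protocol*

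**What the plan says.** **The intervention and the register.** Section 5 describes the partner as "implementing the following policies, activities, and tools in 15 communities". Item 3 of that package reads "At their monthly meetings with RCH staff, CHWs will review the ART register to identify women who missed scheduled appointments". CHWs then try to contact these women, and "CHWs will provide updates to the clinic about their progress". On present practice, Section 4 says that "CHWs in Shinyanga do not participate in any activities related to the provision of HIV care for HIV-infected pregnant women".

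**The outcome.** Section 6.2: "We define retention as a woman who attended her scheduled visit between 60-90 days postpartum". Section 6.4 powers the study on this outcome, from 67% to 80%.

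**The source of the outcome.** For the ART register, Section 7.2 says "we will match them to the ART register to determine whether they initiated ART and attended visits". For CTC2 cards it says "We will abstract data from these cards as needed, to supplement data in the ART register". Table 1 lists the ART register first for retention, followed by CTC2 cards and the CHW register. It assigns the pharmacy logbook to adherence only, although 7.2 says that the logbook holds ART pick-up dates and quantities.

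**A conflicting statement.** The analysis paragraph for Evaluation Question #1 (7.4) says "All three indicators will be measured primarily from ANC records, though we will also back check these records with CHW logs". It also specifies a difference-in-differences analysis of all three measures.

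**The concern.** The activity being tested includes regular work on the record that later measures its success. A monthly search for missed visits could bring to light a woman who attended but was not entered, and the entry might then be completed. Retention is binary, so an attended but unentered visit counts as a loss. Any such completion turns a recorded loss into a recorded success.

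If this happens more in intervention facilities, part of the estimated effect is better bookkeeping. The planned safeguards are weak on this point. CTC2 cards have no stated trigger for use. The only stated cross-check is against CHW logs, which in the intervention arm are kept by the workers delivering the intervention. The limitations section discusses only timing. Genuine re-engagement through tracing is the intended effect and is not in question here.

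**Working it through.** **1. The plan's own figure.** Inputs from Section 6.4: 67% versus 80%, ICC 0.05, 15 communities per arm, 80% power. Two-sided alpha of 0.05 is my assumption, since none is stated. The continuity-corrected two-proportion formula gives 195 per arm under individual randomisation (180 uncorrected). The design effect is 1 + (36 − 1) × 0.05 = 2.75. Then 195 × 2.75 = 536.25, rounded up to 537 per arm, or 537/15 = 35.8, so 36 per community. The stated size reproduces and is not disputed.

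**2. Which record decides retention.** Section 7.2 describes the ANC register as holding ANC visits, HIV test results, delivery and the postnatal visit. It does not mention ART visits at day 60–90. On that description the ART register is the operative source, despite the statement in 7.4.

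**3. How much one entry matters.** Section 6.2 schedules visits at day 42 and every 30 days thereafter, that is days 72 and 102. Only day 72 falls in the 60–90 window, so on schedule a single missing entry decides a woman's outcome.

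**4. What difference-in-differences removes.** Let R be true retention, equal in all four arm-by-period cells (no true effect), and c the share of attended visits entered. Recorded retention is R × c, and the estimate is

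R × [(c intervention, endline − c intervention, baseline) − (c comparison, endline − c comparison, baseline)].

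A stable gap between arms cancels, and so does a change shared by both arms. A change in one arm only does not. Section 7.1 states that the baseline cohort is unexposed, so a change caused by the review would fall in the intervention arm at endline.

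**5. Illustrative size.** R = 0.67 is the plan's comparison rate. The values of c are assumptions.

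| c, intervention endline | c, other three cells | Spurious difference |
|---|---|---|
| 0.90 | 0.90 | 0 |
| 0.95 | 0.90 | 0.67 × 0.05 = 3.35 points |
| 1.00 | 0.90 | 0.67 × 0.10 = 6.7 points |

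These compare with a target of 13 points.

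**6. Effect on error rates.** For an endline-only comparison at the planned size, the effective n is 540/2.75 = 196.4 per arm. The chance of a significant result favouring the intervention is about 10% for the 5-point gap and 28% for the 10-point gap, against a nominal 2.5% in that direction. The planned estimator is different and its standard error is not given. With 36 women per community per cohort, the variance of a community mean is proportional to 0.05 + 0.95/36 = 0.0764. The ratio of the difference-in-differences standard error to the endline-only one runs from √(2 × 0.0264/0.0764) = 0.83, if community effects are fully stable between cohorts, to √2 = 1.41, if they are independent. Dividing the bias-to-SE ratios (0.68 and 1.38) by these factors gives about 7% to 13% for the 5-point gap and 16% to 38% for the 10-point gap. All of these depend on an assumed gap.

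**The case against.** The strongest reply is that the mechanism is inferred. The protocol says that CHWs look through the register to find women and then report back. It does not say that anyone completes or corrects past entries. A reader might infer that the review does correct the register; the text does not establish this. Closer scrutiny could also remove wrong attendance entries, which would push the difference the other way. Section 7.3 notes that some facilities have electronic records, where omissions may differ. This stands, and it is why no size can be claimed.

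A reader might also infer that comparison facilities have no review of missed visits. The documents do not say so. Item 3 allows for tracing by the clinic itself, and the local definition of loss to follow-up already involves follow-up attempts. What the package adds in one arm is the monthly review with CHW participation. This also stands. If clinics in both arms review the register equally well, the gap could be zero.

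Third, it is tempting to quote an inflated false-positive rate for the trial. The documents support none: the omission rates and the standard error of the planned estimator are both missing.

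Finally, one might say that when to consult a supplementary source belongs in an abstraction manual. That is fair for operational detail. But the protocol already fixes data sources in 7.2 and Table 1, and records that are not abstracted cannot be recovered by analysis.

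**Conclusion.** The concern holds as a plausible, unquantified risk of bias in the powered outcome. It is not a demonstrated error. Three things are in the text: register review belongs to the package delivered in the 15 intervention communities, the same register determines attendance, and supplementary records have no uniform rule. It follows that difference-in-differences would not remove a recording change caused by the intervention. Whether such a change occurs, and its size, are unknown. At 67% true retention, an assumed gap of 5 to 10 points in completeness gives about 3 to 7 spurious points, roughly a quarter to a half of the 13-point target; no gap gives none. The conflict between 7.4 and 7.2 with Table 1 over the primary source is a separate matter of wording that must be reconciled. I rate the point a cheap improvement.

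**What to change.** - Keep the Section 6.2 definition of retention as primary. Counting any pick-up in any source as retained would change the powered endpoint.
- In 7.2 and Table 1, replace the as-needed condition for CTC2 cards with one rule for both arms and both cohorts. For example, check the card for every sampled woman with no register entry in the day 60–90 window.
- Report, by arm and period, the share of visits found only outside the ART register. This would help to show whether completeness changed in one arm.
- Add a sensitivity analysis that classifies retention from the pharmacy pick-up dates already abstracted for the medication possession ratio. State how supply dispensed before day 60 is counted.
- Reconcile 7.4 with 7.2 and Table 1 on the primary source.

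**Cost.** Some extra CTC2 abstraction. If 36 women per community applies to each cohort, there are 36 × 30 × 2 = 2,160 women. With 67% recorded as retained, about 0.33 × 2,160 ≈ 713 cards would be checked. The pharmacy data need no new collection. Two limits remain. A check confined to women without an entry finds omissions but not false entries. A pick-up is also not the same event as a scheduled visit, and the protocol does not say that the logbook is unaffected by the intervention. The pharmacy result should therefore stay a sensitivity analysis.
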